### Follow-Up Procedure

The first 5 participants are enrolled for a total of 10 months (an initial 4-month period followed by a 6-month follow-up period) and the other 20 participants for 6 months. An installation visit will take place in the days following enrollment. A remote follow-up evaluation will be carried out over the phone by a CRA every 2 months after the baseline assessment (see Table 2). The last visit will be conducted by the CRA in the participant’s home after 6 months. For the first 5 participants enrolled in the study, the baseline for data analysis is defined as the beginning of the 6-month follow-up period at the end of the first preliminary 4-month period which is dedicated to technical feasibility. The proper regulatory and ethical conduct of the study is monitored by a clinical research technician, acting on behalf of the University Hospital.

**Table 2 table2:** Data collection.

Variables	Preinclusion (CRA^a^, in-person)	Baseline T0 (investigator)	T2 months (CRA, phone)	T4 months (CRA, phone)	T6 months (CRA, in-home visit)
Informed consent	✓	✓	—^b^	—	—
Sociodemographic data	—	✓	—	—	—
ADL^c^, IADL^d^, MMSE^e^	—	✓	—	—	✓
Frailty criteria, SPPB^f^	—	✓	—	—	✓
Acceptability questionnaire, EQ5D^g^	—	✓	✓	✓	✓
Major medical events	—	✓	✓	✓	✓
Sensor data	—	Continuous measures	Continuous measures	Continuous measures	Continuous measures

^a^CRA: clinical research assistant.

^b^Data not collected.

^c^ADL: activities of daily living.

^d^IADL: instrumental activities of daily living.

^e^MMSE: mini mental state evaluation.

^f^SPPB: short physical performance battery.

^g^EQ5D-3L: EuroQol 5D score to describe and value health, quality of life questionnaire.

### Study Measures

The primary aim is to assess the sensitivity and specificity of the solution, defined as the ability to trigger alerts deemed relevant by the recipients: older adults, care partners, and professional support workers. To this end, both conventional and automatic alerts will be recorded during the follow-up period. Following each alert, the CRA gathers subjective feedback from the participant (for automatic alerts only), the care partner, and the telecare worker: *Was it relevant to alert you?* The alerts are also described (number, time of the day, duration of the communication if a communication is established, subject of the call in case of a conventional alert, and solutions proposed).

The secondary aim is to evaluate the ability of the system to detect a functional or cognitive decline and any major event. All major medical events, defined as any event resulting in in-home physician or paramedic intervention, or a call to the emergency services, are collected retrospectively by the CRA every 2 months (by phone).

Sociodemographic and health data are collected at baseline. The participants’ cognitive and functional parameters are assessed at baseline and at the end of follow-up: MMSE (ranging from 0 to 30; the greater the score, the greater the global cognition) [15]; ADL (ranging from 0 to 6, the greater the score; the greater the functional autonomy in daily life) [13]; Instrumental activities of daily living (ranging from 0 to 8; the greater the score, the greater the functional autonomy in daily life, eg, ability to use the telephone) [16]; Cardiovascular Health Study frailty index criteria (unintentional weight loss, self-reported exhaustion, weakness, slow walking speed, and low physical activity) [12]; Short Physical Performance Battery (consisting of a balance test, a 3-m walking test, and a 5 chair-rises test; score ranging from 0 to 12 with 12 indicating the highest degree of functioning) [17].

The acceptability questionnaire is adapted from the Quebec User Evaluation of Satisfaction with Assistive Technology Scale (degree of satisfaction with technology ranging from 1=not satisfactory at all to 5=very satisfactory) [18]; EuroQol questionnaire to describe and assess health (EuroQol questionnaire 5 dimensions, each comprising 3 levels, are summarized into an index ranging from −0.59 to 1, with 1 indicating full health) [19]; and major medical events. Adverse events and their potential imputability to the monitoring procedure are collected by the CRA throughout the study.

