## Introduction

### Background

We are facing an increase in the number of older adults with a high prevalence of functional and cognitive decline [1,2]. Early preventive strategies could stabilize or even prevent this decline [1,3,4]. Most frail older individuals are living at home, and we recognize the difficulties in achieving seamless in-home monitoring for the early detection of subtle health changes over time [1,2]. Clinical assessments are usually performed too far apart and outside the person’s own environment. These evaluations rely on self-reported information affected by recall bias and poor reliability [5]. A follow-up before functional or cognitive impairment could have a positive impact through personalized care plans when symptoms can still be treated.

Technology could potentially help to overcome this shortfall in terms of follow-up by providing continuous sensitive and ecologically valid measures. Several real-life studies confirm the relationship between sensor-based monitoring of physiological parameters and health outcomes [6,7]. The follow-up of health changes over time could also support the living choices made by older individuals and their care partners. Some people abandon their desire for independence in favor of the more reassuring environment of a dedicated living facility much earlier than necessary. Nevertheless, although information and communication technologies have been shown to be effective in many medical situations [8], few solutions are proposed to monitor the intrinsic capabilities of older adults in their own homes [9-11]. Beyond *organ-based* telemonitoring solutions (eg, heart failure or diabetes monitoring), a comprehensive function-based monitoring solution could be beneficial to avoid the overlap and multiplication of technical tools in this complex population.

We hypothesized that a network of low-cost sensors could trigger alerts if an acute and unusual event is detected in activities of daily living—ADL (eg, use of the bathroom at night, followed by several hours of immobility) or subtle changes over time (eg, disorganization in stereotypical habits). Our solution based on nonintrusive sensors could provide relevant information to care partners and health professionals to support the monitoring of older people in their homes, thus promoting independent living.

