### Setting and Participants

All participants must give their written informed consent to take part in the study. Ethical approval was obtained from the Regional Independent Ethics Committee in June 2017 (ID-RCB: 2017-A01002-51).

This solution targets older adults, living with or at risk of functional or cognitive disability and living alone. The detailed inclusion criteria are as follows: aged 75 years or above, living alone at home; frail according to Fried criteria [12] or living with a disability but with an ADL score [13] 3 out of 6 or above; able to walk without help; and provision of written informed consent.

The exclusion criteria are as follows: patient presenting a Mini Mental State Examination (MMSE) <16 out of 30 and without daily care partner support; and under curatorship or guardianship.

Study participants are enrolled through a prescreening procedure on the basis of public administrative records held by several town halls in the region (person aged 75 years or above, living alone at home, and able to walk without help). A clinical research assistant (CRA) then conducts a preinclusion visit by phone. The inclusion visit with the principal investigator (AP) takes place in the Geriatrics Unit at the Toulouse University Hospital.

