### Statistical Analysis

The main analysis will be an intent-to-treat analysis. The quantitative outcomes will be estimated with 95% CI. Quantitative variables will be expressed by mean values and standard deviations. The 6-month follow-up period for the 25 participants will allow us to record the number and frequency of alerts generated by the solution. A total of 3 positive predictive value (PPV) calculations (estimation of legitimate alerts) will be done (95% CI, thanks to end users’ feedback for the overall follow-up period and for each 2-month follow-up period: 0-2 months, 2-4 months, and 4-6 months) to estimate the progression of algorithm performance. For the secondary objective, we will also analyze these 3 periods to evaluate the performance of the automatic alerts in detecting changes in functional or cognitive autonomy or major events (sensitivity, specificity, predictive value, and receiver operating characteristic [ROC] curves). Alerts will be addressed with both a binary approach (no alert vs 1 alert to estimate sensibility, specificity, PPV, and negative predictive value) and a continuous approach (number of alerts over the period to plot an ROC graph and estimate the area-under-the-curve). The Department of Epidemiology at our University Hospital will conduct statistical analyses using SAS version 9.4 (SAS Institute, Inc).

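### The major medical event is defined by the route of the response, so hospital events reached another way count as no event, and an alert can itself create a qualifying event

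*Protocol article*

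**What the plan says.** Study Measures words the major-event endpoint thus: "defined as any event resulting in in-home physician or paramedic intervention, or a call to the emergency services, are collected retrospectively by the CRA". The definition does not name hospital admission, arrival at an emergency department by other means, or death.

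The same section has the clinical research assistant (CRA) collect these events retrospectively every two months by phone. Follow-Up Procedure differs slightly for the final contact: "The last visit will be conducted by the CRA in the participant’s home after 6 months". The look-back is two months either way.

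Statistical Analysis then uses the events as a reference standard. For the three two-month periods the plan is to "evaluate the performance of the automatic alerts in detecting changes in functional or cognitive autonomy or major events (sensitivity, specificity, predictive value" and ROC curves). Discussion (Strengths and Limitations) says this analysis should help to size a future study.

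Procedure describes what follows an alert. Sensor-based alerts go to a telecare worker, whose possible responses run from contacting the participant, through phoning the care partner, to phoning emergency services.

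**The concern.** The definition sorts events by who responded, not by what happened to the participant. Two events of equal gravity can be classified differently: one that brings paramedics to the door is an event, while one that a relative drives to hospital is not.

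In an accuracy analysis this is misclassification of the reference standard. An alert that correctly preceded an omitted admission moves from true positive to false positive. A period with an omitted event and no alert moves from false negative to true negative. The first move lowers PPV, and the net effect on specificity is a small fall.

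The second problem runs the other way. If an alert prompts a call to emergency services, that call satisfies the definition whatever is then found. The alert can supply its own confirmation, which pushes PPV and sensitivity up. The two effects do not reliably cancel, and the plan has no step that would separate them.

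**Working it through.** **The plan's own figure.** The article gives no expected figure for the major-event analysis. Its one precision example (Sample Size: 50 alerts, half valid, 35.5% to 64.5%) reproduces as the exact binomial interval for 25/50, 35.53% to 64.47%. That example concerns user-rated relevance, the primary outcome, and does not bear on this point.

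**Inputs.** From the article: 25 participants × 3 two-month periods = 75 participant-periods. Assumed, because the article gives no values: 20 periods with a true event, alert sensitivity 60%, specificity 70%, and 30% of events falling outside the definition regardless of alerts. The count of 75 is approximate, since Procedure has no automatic alerts in the first (learning) month.

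**All events counted.**
- True positives 20 × 0.6 = 12; false negatives 8.
- False positives 55 × 0.3 = 16.5; true negatives 38.5.
- PPV = 12/28.5 = 42%. Specificity = 38.5/55 = 70%.

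**30% of events outside the definition.**
- True positives 12 × 0.7 = 8.4; false negatives 8 × 0.7 = 5.6.
- False positives 16.5 + 3.6 = 20.1; true negatives 38.5 + 2.4 = 40.9.
- PPV = 8.4/28.5 = 29%. Specificity = 40.9/61 = 67%. Sensitivity = 8.4/14 = 60%, unchanged.

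In general, if a fraction m of events is omitted regardless of alerts, observed PPV = true PPV × (1 − m).

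**Range under other assumptions** (sensitivity 70%, specificity 80%):

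| Periods with an event | PPV, none omitted | PPV, 20% omitted | PPV, 40% omitted |
|---|---|---|---|
| 10% | 28.0% | 22.4% | 16.8% |
| 20% | 46.7% | 37.3% | 28.0% |
| 30% | 60.0% | 48.0% | 36.0% |

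In the 20% row, specificity goes from 80% to 77.6% and then to 75.5%; NPV rises from 91.4% to 93.1% and then to 94.9%.

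**Alert-created events.** Return to the first table with all events counted. Suppose one alert in an otherwise event-free period leads to an emergency call. That period moves from false positive to true positive:
- PPV = 13/28.5 = 46%, up from 42%.
- Sensitivity = 13/21 = 62%, up from 60%.
- Specificity = 38.5/54 = 71%, up from 70%.

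How often this would happen cannot be derived from the article.

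**The case against.** **Weight.** This is a secondary analysis in 25 people; the primary outcome is user-rated relevance. In the illustration the PPV shift of about 13 points is smaller than the approximate 95% half-width around 12/28.5, 1.96 × √(0.421 × 0.579/28.5) = 18 points. The article discloses its reliance on retrospective correlations, and it says that other studies in comparable populations can supply the future sample size. All of this stands and keeps the point modest. It does not close the gap, because the shift is systematic and the definition is explicit.

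**Other data streams.** Adverse events are collected throughout the study and might recover some omitted events. The article states no link between them and this endpoint.

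**A stronger reading on recall.** A reader might infer that forgotten events are lost as well. The study "This solution targets older adults, living with or at risk of functional or cognitive disability and living alone", and the Background says of usual assessments: "These evaluations rely on self-reported information affected by recall bias and poor reliability". The article does not establish such a loss. It does not say who is interviewed, and the full protocol may. The exclusion covers a "patient presenting a Mini Mental State Examination (MMSE) <16 out of 30 and without daily care partner support", so the most impaired participants have a possible informant. The Background sentence is about infrequent clinical assessments, not recall of a paramedic visit. The last contact is in the home.

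**A stronger reading on unequal capture.** A reader might also infer that events near alerts are better captured because the CRA seeks feedback after each alert. That feedback asks about relevance, and the participant is asked only after automatic alerts. Nothing says that medical events are elicited there. Capture of 90% with an alert against 60% without would turn a sensitivity of 60% into 10.8/15.6 = 69%, but those rates have no basis in the article.

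**Conclusion.** The point holds for the definition. As written, an unplanned hospital admission or emergency attendance that involved neither a home visit nor an emergency call is scored as no event, and no other part of the article repairs this. The direction is clear when omission is unrelated to alerts: PPV falls in proportion to the share omitted, specificity falls slightly, NPV rises and sensitivity is unchanged. The size is unknown; the fall from 42% to 29% rests wholly on assumed inputs.

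It also holds that the reference standard is not independent of the alert, because an emergency call prompted by an alert qualifies as an event. That bias is in the opposite direction and is also of unknown size.

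Recall loss and better capture around alerts are possible but not shown, and should not be reported as established defects. The primary objective is untouched. The change is worth making because it is cheap and gives a cleaner reference standard.

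**What to change.** 1. Keep the existing criteria, including emergency calls, and add death and any unplanned hospital admission or emergency department attendance, whatever the route.
2. At the existing T2, T4 and T6 contacts, ask the participant, and the care partner where there is one, about these events and their dates. Use the same questions whether or not an alert occurred.
3. Flag each event whose qualifying call or visit was triggered by an alert, and repeat the accuracy analysis without counting those events. Some will be genuine events that the alert found, so this second analysis may understate performance; show both.
4. Because the first phase is complete and the study is under way, report results under the published definition as a sensitivity analysis, so that a change of definition part-way is visible.

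The cost is one or two extra questions per contact and two definitions to report. A check against hospital or general-practitioner records would be an optional extra; it may need further consent from people already enrolled and is not required for this fix.

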### Sample Size

To the best of our knowledge, no comparable study has evaluated a similar primary endpoint in this population. Therefore, a formal sample size calculation could not be carried out. However, we can expect more than 1 alert per individual during the 6-month period. The predictive value calculations (estimation of legitimate alerts) will be based on numbers over 25, a 95% CI accuracy of at least ±20%. As an example, if a participant triggers 2 alerts on average during the study, with half of them rated as valid, a 95% CI close to 35.5% to 64.5% can be expected.

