**Methods:**

The primary outcome will be evaluated for each successive 2-month follow-up period to estimate the progression of our learning algorithm performance over time. In total, 25 frail or disabled participants, aged 75 years and above and living alone in their own homes, will be enrolled for a 6-month follow-up period.

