## Methods

### Study Design

This is a prospective open-label study. We will enroll 25 participants for a 6-month follow-up period. To allow for modifications to the solution in the event of technical issues before wider use, the first 5 participants are enrolled for a preliminary 4-month phase before the 6-month regular follow-up period. The enrollment process is spread out over time for the same reason. The flow chart is presented in Figure 1.

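### The stated precision of ±20% or better holds for the overall 6-month PPV but not, at the protocol's own example, for the 2-month PPVs that are also part of the primary outcome

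*Protocol article*

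**What the plan says.** The Sample Size section of the protocol article explains that no formal calculation was possible. It then offers a precision statement. The starting point is that "we can expect more than 1 alert per individual during the 6-month period". From this it concludes that the predictive value calculations "will be based on numbers over 25, a 95% CI accuracy of at least ±20"%. Its illustration supposes 2 alerts per participant over the study, half of them judged relevant. For that case the section reports that "a 95% CI close to 35.5% to 64.5% can be expected".

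The Study Design section gives the number of people: "We will enroll 25 participants for a 6-month follow-up period".

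On what is estimated, the Methods part of the Abstract says: "The primary outcome will be evaluated for each successive 2-month follow-up period to estimate the progression of our learning algorithm performance over time". The Objectives section puts the evolution of the algorithm's performance in the primary objective, next to the relevance of the alerts. The Statistical Analysis section plans PPVs with 95% confidence intervals for the whole follow-up and "for each 2-month follow-up period: 0-2 months, 2-4 months, and 4-6 months".

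Two further statements affect how alerts spread over the periods. The Procedure section says that the platform issues no automatic alerts in the first month, while the algorithm learns. The Follow-Up Procedure section sets the analysis baseline of the first 5 participants after a 4-month preliminary phase, so their learning month may already be over at baseline.

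**The concern.** The precision claim speaks of the predictive value calculations in general, but its denominator is the number of alerts pooled over 6 months. The same section gives no figure for a 2-month period. A period receives only part of the alerts, and the first period may receive the smallest part.

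The per-period PPVs are how the study means to show whether the algorithm improves. If their precision is much worse than the one printed, a reader may take a chance difference between periods for learning. Equally, a reader may take three wide, overlapping intervals as evidence that nothing was learned.

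**Working it through.** **Inputs.** 25 participants (Study Design). More than 1 alert each as the expectation, and 2 each with half rated relevant as the example (Sample Size). Two-sided 95% intervals and three 2-month periods (Statistical Analysis). The split of alerts over periods is not in the document. I assume a constant alert rate and show three splits.

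**Formulas.** Exact (Clopper-Pearson) interval for x relevant alerts out of n: lower limit = 2.5% quantile of Beta(x, n−x+1), upper limit = 97.5% quantile of Beta(x+1, n−x). Normal approximation: half-width = 1.96 × √(p(1−p)/n).

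**Step 1: the protocol's own figures.**
- 25 × 2 = 50 alerts, 25 relevant. The exact interval is 35.5% to 64.5% (±14.5), which is the printed interval. The normal approximation would give ±13.9, so the protocol's method is the exact one.
- 25 × 1 = 25 alerts at PPV 50%. The normal approximation gives 1.96 × 0.5/√25 = ±19.6. Exact half-widths are ±20.4 (12/25), ±20.1 (13/26) and ±19.7 (13/27).

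Both statements therefore reproduce, the ±20 to within rounding, for the 6-month total.

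**Step 2: the same 50 alerts by period, PPV 50%, exact intervals.**

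| Assumed split | Alerts in months 0-2 / 2-4 / 4-6 | Half-width (points) |
|---|---|---|
| Equal thirds (50/3 = 16.7) | 16 or 17 in each | ±25.3 (8/16) or ±24.6 (8/17) |
| Month 1 silent for all 25 (live months 25/50/50) | 10 / 20 / 20 | ±31.3 / ±22.8 / ±22.8 |
| Month 1 silent for 20, not for the first 5 (live months 30/50/50) | 11.5 / 19.2 / 19.2 | about ±29 / ±23 / ±23 |

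The third row is 50 × 30/130 = 11.5 and 50 × 50/130 = 19.2. Its half-widths use the Beta quantile with non-integer counts. No period has more than 25 alerts and none reaches ±20.

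**Step 3: the expected minimum.** 25 alerts over three equal periods is 25/3 = 8.3 each, which gives about ±34 (4/8: ±34.3).

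**Step 4: sensitivity.**
- PPV 80%: 16/20 gives ±19.0 and 14/17 gives ±19.8, so such periods just reach ±20. With 8/10 the half-width is still ±26.5.
- Wilson intervals at PPV 50%: ±20.1 (n = 20), ±21.4 (n = 17), ±22.0 (n = 16) and ±26.3 (n = 10). They are narrower but still above ±20.

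**Step 5: change from first to last period, PPV 50% in both, independent alerts.** Half-width = 1.96 × √(0.25/n₁ + 0.25/n₃).
- 16.7 vs 16.7: 1.96 × √0.0300 = ±33.9
- 11.5 vs 19.2: 1.96 × √0.0347 = ±36.5
- 10 vs 20: 1.96 × √0.0375 = ±38.0

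**Step 6: alerts needed for ±20 in every period.** About 27 per period at PPV 50% (exact ±19.7). Equal thirds: 3 × 27 = 81, or 81/25 = 3.2 per participant. If month 1 is silent, the first period holds 10/50 to 11.5/50 of the alerts. The total is then 27 × 50/10 = 135 (5.4 per participant), or 27 × 130/30 = 117 (4.7 per participant).

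**The case against.** The strongest reply is that there is no arithmetic error. A reader might infer one, but the printed interval and the ±20% both reproduce, and the section ties its count to the 6-month period. It never says expressly that ±20% applies to each 2-month PPV. This stands: the fault is one of scope. The claim is nevertheless worded for the predictive value calculations without restriction, and no other precision is given for the per-period ones.

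A reader might also infer that the study's main quantity has no valid precision statement. That goes too far. The Statistical Analysis section plans the overall PPV as well, and the figure for it is sound.

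Third, 2 alerts per participant is only an example, the section disclaims a formal sample size, and PPV 50% is the widest case. At a PPV of 80%, periods with 17 to 20 alerts do reach ±20. This also stands, but a first period of 10 alerts would still miss it. The minimum rate that the protocol actually expects makes matters worse.

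Fourth, manual alerts by button or intercom can occur in the first month. The splits with a silent first month therefore apply to automatic alerts, the ones that show how the algorithm performs. Without those splits, equal thirds still gives about ±25.

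Finally, a reader might infer that progression will be judged by comparing intervals by eye, or that no model of change is planned. The article says neither. Such a model may sit in the statistical analysis plan, which is not shown, so its absence here is not an error.

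**Conclusion.** The concern holds as a matter of scope. The precision in the Sample Size section is correct for the overall 6-month PPV and is not delivered for the 2-month PPVs. At 50 alerts and PPV 50%, the per-period half-widths run from about ±23 to ±31 points, depending on the split. At one alert per participant and equal thirds, the figure is about ±34. The change from first to last period is known only to about ±34 to ±38 points, so a 30-point improvement would lie within its margin of error.

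These figures assume a constant alert rate, exact intervals for each PPV, the normal approximation for the change, and independent alerts. Positive correlation between alerts from the same person would widen them. A PPV well above 50% would narrow them, enough to reach ±20 in the larger periods only. The point should be corrected, but it does not undermine the overall estimate.

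**What to change.** In the Sample Size section, limit the ±20% and the 35.5% to 64.5% (±14.5) figures to the overall PPV. Add a separate statement for the 2-month PPVs: about ±23 to ±31 points at 50 alerts and PPV 50%, naming the assumed split over the periods, and wider if alerts cluster within participants.

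As an optional improvement, report the change in PPV between periods with its own 95% confidence interval, allowing for repeated alerts from the same participant, and keep the three PPVs as description.

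The cost is a less favourable printed figure and, if the option is taken, one more analysis. No additional participants or data collection are needed.

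### The example interval of 35.5% to 64.5% counts 50 repeated alerts from 25 people as independent, so it is a best case for the precision of the PPV

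*Protocol article*

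**What the plan says.** The Study Design section sets the number of people: "We will enroll 25 participants for a 6-month follow-up period". The Sample Size section explains that no formal calculation was possible and offers precision instead: "The predictive value calculations (estimation of legitimate alerts) will be based on numbers over 25, a 95% CI accuracy of at least ±20" percent. It illustrates this with a case of 2 alerts per participant on average: "with half of them rated as valid, a 95% CI close to 35.5% to 64.5% can be expected".

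The Study Measures section makes the alert the unit of rating: "Following each alert, the CRA gathers subjective feedback from the participant (for automatic alerts only), the care partner, and the telecare worker". One participant can therefore contribute several ratings, each involving that same participant and care partner.

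The Statistical Analysis section plans the PPV with 95% CIs, overall and by 2-month period: "A total of 3 positive predictive value (PPV) calculations (estimation of legitimate alerts) will be done". It does not say how the intervals will be computed. The article nowhere mentions within-participant correlation, a design effect, or a limit of one alert per participant for the PPV.

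**The concern.** Alerts from one participant share a home, a behavioural baseline learned in the first month, and the participant and care partner who rate them. Their relevance ratings are likely to be positively correlated. In that case 50 alerts from 25 people carry less information than 50 alerts from 50 people, and less still if a few participants generate most of the alerts.

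This matters because, without a formal sample size calculation, these precision statements are the only quantitative support for 25 participants, and they concern the primary endpoint. The PPV is also to be compared across periods to judge whether the algorithm improves. An understated interval could make a change in which participants are alerting look like a change in performance.

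**Working it through.** **Inputs from the article.** 25 participants; mean 2 alerts each, so 25 × 2 = 50 alerts; half valid, so 25 of 50; stated interval 35.5% to 64.5%, a half-width of 14.5 points; target ±20 points.

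**Step 1: reproduce the stated figure.** For 25 of 50 independent alerts:

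- Clopper-Pearson (exact): lower = Beta quantile(0.025; 25, 26) = 35.53%; upper = Beta quantile(0.975; 26, 25) = 64.47%. This matches.
- Wald: 36.1% to 63.9%. With continuity correction: 35.1% to 64.9%. Wilson: 36.6% to 63.4%. None of these matches.

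The ±20 points at about 25 alerts fits the same independent model: 1.96 × √(0.25/25) = 19.6 points. The arithmetic is right; independence is built into it.

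**Step 2: allow for correlation.** The ICC and the spread of counts are assumptions, since the article gives neither. With mean count m = 2 and coefficient of variation CV of the counts:

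- Design effect = 1 + [(1 + CV²) × m − 1] × ICC
- Half-width ≈ 1.96 × √(0.25 × design effect / 50) = 13.9 points × √(design effect)

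Three patterns of counts:

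- Exactly 2 each: CV² = 0, design effect = 1 + ICC.
- Poisson with mean 2: CV² = 2/4 = 0.5, design effect = 1 + 2 × ICC.
- Overdispersed (negative binomial, mean 2, variance 6): CV² = 6/4 = 1.5, design effect = 1 + 4 × ICC.

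The table also gives half-widths and coverage from beta-binomial simulation with a true PPV of 50%. Coverage is that of the exact binomial interval when it ignores clustering. The half-widths come from 4,000 runs per cell and the coverage from 5,000.

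| Counts | ICC | Design effect | Half-width, formula (points) | Half-width, simulated (points) | Coverage of nominal 95% interval |
|---|---|---|---|---|---|
| Exactly 2 | 0.1 | 1.1 | 14.5 | – | 95.6% |
| Exactly 2 | 0.3 | 1.3 | 15.8 | – | 94.0% |
| Exactly 2 | 0.5 | 1.5 | 17.0 | – | 92.2% |
| Poisson | 0.1 | 1.2 | 15.2 | 15.1 | 94.3% |
| Poisson | 0.3 | 1.6 | 17.5 | 17.7 | 90.4% |
| Poisson | 0.5 | 2.0 | 19.6 | 19.5 | 85.8% |
| Overdispersed | 0.1 | 1.4 | 16.4 | 16.5 | 92.2% |
| Overdispersed | 0.3 | 2.2 | 20.6 | 20.4 | 85.0% |
| Overdispersed | 0.5 | 3.0 | 24.0 | 23.7 | 78.1% |

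An exact interval at the effective sample size (50 / design effect) is slightly wider: 15.2 to 17.7 points with exactly 2 alerts each and 15.9 to 20.5 with Poisson counts.

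**Step 3: compare with ±20.** With equal counts the target is met across the assumed range. With Poisson counts it is borderline at ICC 0.5 (19.6 points by the formula, 20.5 by the exact method). With overdispersed counts it is missed from an ICC of about 0.3.

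**Step 4: more alerts per person.** The article expects more than 1 alert per individual and sets no upper figure. Assume 10 each, so 250 alerts. A simple binomial half-width is then 1.96 × √(0.25/250) = 6.2 points. The simulated true half-width over ICC 0.1 to 0.5 is 8.8 to 15.3 points (Poisson) or 10.6 to 19.8 (overdispersed). At ICC 0.3 the simple interval covers about 69% (Poisson) or 56% (overdispersed). True precision stays within ±20 points here, but a simple binomial interval would greatly overstate it.

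**The case against.** The strongest defence is that the figure is offered as an example with hedged wording, that the sample size was not derived from it, and that no hypothesis test or decision threshold depends on it. The precision the plan commits to is ±20 points, and most of the assumed range respects that. With exactly 2 alerts each and an ICC of 0.1 the loss is negligible, because the conservatism of the exact interval absorbs it. All of this stands. It lowers the weight of the point but does not remove it: the example is still presented as what can be expected, with no mention that it assumes independence.

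A reader might go further and infer that the planned PPV intervals are too narrow. The article does not support that. The Statistical Analysis section names no method, and an analysis plan that is not shown could specify a clustered one. Independence is demonstrated only for the Sample Size figures. At the example rate, each 2-month period has about 2/3 = 0.67 alerts per person, and even a simple exact interval would then cover about 92% to 97% over the same ICC range.

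Two further inferences go too far. The article does not say that each participant has a personal algorithm; it refers the algorithm to another source. Nor are all raters constant: the telecare worker sits on a nationwide platform staffed around the clock and may differ from alert to alert. Performance that changes with feedback could also weaken the within-person correlation. These points make the size of the ICC uncertain, but shared homes, participants and care partners still make some positive correlation the natural expectation.

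**Conclusion.** The point holds for the Sample Size section. The stated 35.5% to 64.5% assumes 50 independent alerts, while the design yields repeated ratings from at most 25 people, so it is a best case. Over an assumed ICC of 0.1 to 0.5 at a mean of 2 alerts, the realistic half-width runs from about 15 points, hardly different from the 14.5 stated, to about 24 points when counts are overdispersed. How evenly alerts are spread over participants matters as much as the ICC.

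For the Statistical Analysis section the point is conditional: coverage would fall below nominal only if simple binomial intervals were used, and would fall further if alerts per person were numerous.

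This should be fixed, but it is not critical: the study is descriptive, the figure is illustrative, and the ±20-point target fails only in the less favourable scenarios.

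**What to change.** In Sample Size, state that 35.5% to 64.5% assumes independent alerts, and add the range under named assumptions: for an ICC of 0.1 to 0.5 and a mean of 2 alerts, a half-width of about 15 to 17 points with equal counts, 15 to 20 with Poisson counts and 17 to 24 with overdispersed counts.

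In Statistical Analysis, specify that the 95% CIs for the PPV treat the participant as the cluster, with a method suited to about 25 clusters. One choice is a logistic GEE with a small-sample-corrected robust standard error; an independence working correlation keeps the estimate equal to the pooled proportion. A plain percentile cluster bootstrap is less attractive, since in simulation with 25 clusters it covered about 92% to 94%.

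Clustering corrects the interval only. It does not stop one or two heavy alerters from dominating the pooled PPV, which is a separate question of weighting.

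The cost is a slightly less favourable stated interval and a few lines of analysis text. No extra data or participants are needed.
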